##### Ophthalmic exam (standard care; group 2A and 2B) – C0

All children at risk of VPD will be referred to the Pediatric Ophthalmology Department to evaluate visual acuity, refractive error and ocular alignment. This evaluation is performed by ophthalmologists and/or research orthoptists. The total duration of the exam is approximately 1 hour.

##### VFA, (standard care, groups 2A and 2B) – D0

All children at risk of VPD will undergo an extensive VFA. This assessment is part of standard care and will be done by an experienced orthoptist or optometrist. All assessments will be performed according to a standardized protocol that ensures similar assessments, choice of tests and scoring by the various examiners. The following functions will be assessed: ocular alignment and fixation preference, binocular vision, presence of nystagmus, oculomotor function (fixation, saccades, pursuit, motility), convergence, visual acuity, visual field, contrast sensitivity and color vision. Performance per function is classified as normal or abnormal for the child’s age.

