### Outcome measures

To answer our main research question about the effectiveness of early visual intervention in young preterm children, we will compare visual outcomes between the intervention and control group. We will analyze results from the eye tracking-based visual assessment and the additional VFAs at baseline and at yearly follow-up measurements. Primary outcomes are the changes in visual parameters after the duration of the intervention study (i.e., from baseline to follow-up T1 and/or T2), namely quantitative visual parameters (eye tracking-based visual detection and viewing reaction times) and VFA (visual acuity, contrast sensitivity, visual field, ocular motility).

Endpoints are the changes in these parameters after the visual intervention program. These parameters are chosen since their combination provides quantitative and objective results about functional viewing behavior (the eye tracking-based assessment) and clinically relevant visual function outcomes (i.e., the VFAs). In addition, we will compare the effectiveness of direct (at 1 year CA) versus postponed visual habilitation (at 2 years CA) by comparing visual outcomes between these groups at T2.

Secondary outcomes are the neurodevelopmental level at the first follow-up (T1) and results from parental questionnaires about daily visual functioning at T1 and/or T2, i.e., total score, cognitive and motor sub scores of the neurocognitive assessment with Bayley Scales of Infant and Toddler Development (Bayley-III-NL) and total score and sub scores per visual domain of the PAI-CY 0–2 Inventory (i.e., attachment, stimulus processing, orientation, play, mobility, communication). These measures were chosen because Bayley-III-NL is the only available neurocognitive assessment for children at this age, and the PAI-CY 0–2 Inventory is the only available parental questionnaire about daily (visual) behavior at this age.

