### Statistical analyses

#### Sample size calculation

To answer our primary research question about the effectiveness of early visual intervention programs on visual attention and processing functions in preterm children at risk of VPD, we use a repeated measures analysis of variance (ANOVA) for the parameter RTF as primary analysis. An a priori power analysis provided a recommended total sample size of 32 children (and an actual power of 0.81 and a critical F of 4.17).

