#### Effectiveness of visual intervention program

In children at risk of VPD who have been allocated to a visual intervention group, differences in viewing behavior parameter RTF between T0 and T1 are analyzed with a Repeated Measures ANOVA. A *p* value of 0.05 will be considered statistically significant. Covariates are the medical (perinatal and ophthalmic) and demographic factors and the repeated measures analyses will be done with and without them to obtain their contribution to the main effect. All analyses are done according to the intention-to-treat principle.

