#### Other effects of visual intervention on VPD (other parameters)

Secondary study parameters are the differences in other eye tracking-based parameters of viewing behavior and the outcomes of VFAs (e.g., visual acuity, contrast sensitivity, extent of visual field). Repeated measures ANOVAs with a *P* value of 0.05 will be considered statistically significant. After finding a main effect of group on the viewing behavior parameters, post-hoc comparisons will be done to establish which of the five visual stimuli significantly differ from each other in parameter values. For these comparisons, Bonferroni’s correction will be applied to the viewing behavior variables to correct the *P* value for the number of comparisons.

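### VFA results are scored normal/abnormal, but the plan does not say whether the class or the measured value enters its repeated measures ANOVA, which tests change without conditioning on T0 and so wastes power

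*Protocol article*

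**What the plan says.** The VFA section (D0) lists the functions examined and ends with the scoring rule, judged against the child's age: "Performance per function is classified as normal or abnormal". No other scale, unit or score is stated for the VFA.

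Outcome measures places "VFA (visual acuity, contrast sensitivity, visual field, ocular motility" among the primary outcomes and defines the endpoints as changes from baseline. The analysis section on other effects of the intervention says: "Secondary study parameters are the differences in other eye tracking-based parameters of viewing behavior and the outcomes of VFAs". Its examples appear in "the outcomes of VFAs (e.g., visual acuity, contrast sensitivity, extent of visual field", and the method is "Repeated measures ANOVAs with a" significance level of 0.05. No method for binary data is named.

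The power statement under Statistical analyses, "a recommended total sample size of 32 children (and an actual power of 0.81 and a critical F of 4.17", concerns reaction time to fixation (RTF) only. The separate sample size section expects at least 50 eligible children.

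**The concern.** The stated scale and the stated method do not obviously belong together. Three different analyses fit the text: ANOVA on measured acuity, contrast sensitivity or field; ANOVA on 0/1 classes; or a mixture across functions. For ocular motility, which Outcome measures names as an endpoint, no measured value is evident, so the ANOVA would run on a class.

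Whichever scale is meant, a two-group, two-time ANOVA on changes does not use the T0 result as a covariate, although the trial collects it in every child at risk. The sample is small (32 by the RTF calculation, about 50 by the recruitment forecast), and nothing in the article supports power for VFA. These are the outcomes that Outcome measures relies on for clinical relevance, so avoidable loss matters here.

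**Working it through.** **The plan's own figure.** The critical F for 1 and 30 degrees of freedom at 0.05 is 4.171. This matches the stated 4.17 and confirms two groups with N=32. The effect size and correlation are not given, so N and power cannot be rebuilt. The figure concerns RTF and says nothing about VFA.

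**Reading of the test.** The endpoints are changes, so I take the relevant ANOVA term to be group by time. With two times this is identical to the t test on T1 minus T0.

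**Assumed inputs** (the article gives no VFA rates):
- 1:1 allocation, with 16 or 25 children per arm.
- Abnormal at T0: 50% in both arms. Abnormal at T1: 50% in the control arm, 20% in the direct arm.
- The two results come from cutting normal variables with correlation 0.5.

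**Hand check: change-score test.**
- Control: P(abnormal at both) = 1/4 + arcsin(0.5)/(2π) = 0.333. Changes of −1 and +1 each have probability 0.500 − 0.333 = 0.167, so the variance of change is 0.333.
- Direct: P(abnormal at both) = 0.156. P(−1) = 0.344, P(+1) = 0.044, mean −0.30. Variance = 0.344 + 0.044 − 0.09 = 0.297 (unrounded inputs).
- SE = √((0.333 + 0.297)/n) = 0.199 at n=16 and 0.159 at n=25. Effect/SE = 0.30/0.199 = 1.51 and 0.30/0.159 = 1.89. Noncentral t power: 0.31 and 0.46.

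**Hand check: conditioning on T0.**
- Control: P(abnormal at T1) is 0.667 if abnormal at T0 and 0.333 if normal. Within-stratum variance is 0.222.
- Direct: 0.313 and 0.087. Mean within-stratum variance = 0.5(0.313×0.687) + 0.5(0.087×0.913) = 0.147.
- SE = √((0.222 + 0.147)/n) = 0.152 and 0.122. Effect/SE = 1.97 and 2.47. Approximate power: 0.48 and 0.68.

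**Simulation** (40,000 trials per setting, same assumptions):

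| Test | N=32 | N=50 |
|---|---|---|
| Repeated measures ANOVA on 0/1 | 0.30 | 0.46 |
| Mantel-Haenszel stratified on T0, no continuity correction | 0.45–0.46 | 0.65 |
| Linear model on T1 adjusted for T0 | 0.46 | 0.65–0.66 |
| Mantel-Haenszel with continuity correction | 0.29 | 0.52 |

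The linear adjusted model matches the stratified binary test, so linearity is not the cause. A like-for-like logistic group-by-time test agrees: over three effect patterns and latent correlations of 0.3, 0.6 and 0.8, ANOVA power minus logistic power ran from −0.03 to +0.09.

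**Type I error.** At 30% abnormal with no effect, the ANOVA and the uncorrected stratified test both have levels of about 0.045 to 0.049.

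**Rare abnormalities.** At 5% abnormal and N=32, the ANOVA level is about 1.6% to 2.1%, and in 8% to 10% of trials no child changes in either arm, so F is undefined. At N=50 the undefined share is about 2% to 3%. The stratified test is no cure: its level at 5% and N=32 is about 0.5%.

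**Cost of analyzing the class where a value exists.** An effect with about 0.81 power as a measured change at 16 per arm falls to 0.16–0.51 once scored normal/abnormal (20% to 70% abnormal at T0, latent correlation 0.5 or 0.7).

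**The case against.** The best defense is that the D0 sentence describes a standard-care examination and does not define the analyzed variable. The eye tracking section also ends in a normal/abnormal classification, yet RTF is analyzed as a value. Acuity is expressed numerically in the exclusion criteria, and extent of visual field is by its wording a quantity. On that reading, ANOVA suits the three examples given, and the choice of scale could sit in a fuller document. This stands in part: the article does not fix every VFA endpoint as binary. It still never says which form is used, and the defense does not reach ocular motility or the missing adjustment for T0.

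Some stronger readings are tempting but not supported:
- A reader might infer that ANOVA loses power because it is a method for continuous data. The checks above show otherwise.
- A reader might call the estimate uninterpretable. On 0/1 data it is the between-arm difference in change of the proportion abnormal.
- A reader might say that children normal at T0 contribute only noise. They can worsen: under the assumed rates, 33% of such controls and 9% in the direct arm are abnormal at T1. Dropping them cuts stratified power from 0.46 to 0.29 at N=32.
- A reader might blame ANOVA for failing with rare abnormalities. That is a sparse-data limit shared by the alternatives. Plain logistic models met separation in 3% to 59% of simulated trials at 16 per arm.

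**Conclusion.** The point holds as an ambiguity of scale plus an inefficient test. Under the stated assumptions, conditioning on T0 raises power by about 0.16 at N=32 (0.46 − 0.30) and 0.19 at N=50 (0.65 − 0.46). Over other assumed rates and correlations, the gain from baseline-adjusted analyses was about 0.09 to 0.23. The validity of the ANOVA is not in question at moderate abnormality rates, and its failure at about 5% is occasional. All power figures rest on assumed rates, and the gain at N=32 disappears if a continuity correction is used. The point is worth correcting but does not undermine the RTF analysis. Separately, VFA is called primary under Outcome measures and secondary in the analysis section; the two should be reconciled.

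**What to change.** In the section on other effects of the intervention:
1. State for each VFA function whether the measured value or the class is analyzed.
2. Where a value is recorded (acuity, contrast sensitivity, extent of visual field), analyze that value at T1 by ANCOVA adjusting for T0, instead of its class.
3. For functions recorded only as normal/abnormal, such as ocular motility, compare arms at T1 conditioning on T0 status. Use Mantel-Haenszel, without continuity correction when counts are adequate, and an exact or penalized method when sparse. Report the risk difference with a confidence interval.
4. Report very rare abnormalities descriptively, without a test.

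The cost is a change of wording. T0 and T1 assessments are already planned, so no new data are needed wherever the measured values are being recorded.

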#### First follow-up (T1)

Starting at 1 year after inclusion, i.e., from 2 years CA, the following assessments are repeated:

##### Visual screening (study-specific; all groups) – A1

The visual assessment (eye tracking-based exams) will be repeated for all included children and will be combined with an existing appointment for standard outpatient visits at the Neonatology Department.

##### Inventory for daily life visual functioning (study specific) – B1

Parents are asked to complete the inventory again around the time of first follow-up.

##### VFA (standard care) – D1

The VFAs will be repeated in the children at risk of VPD (independent of the visual intervention group they are in), as part of standard care at the visual advisory center.

##### Neurodevelopmental assessment (standard care) – E

From 2 years CA, all children will receive a neurodevelopmental assessment at the NICU as part of the standard follow-up program of the Department of Neonatology. This assessment consists of the Bayley Scales of Infant and Toddler Development (Bayley-III-NL) and is performed by experienced (neuro)psychologists.

#### Second follow-up (T2)

Two years after inclusion, i.e., from 3 years CA, all included children will repeat the eye tracking-based visual screening (A2) and the inventories for daily life visual functioning (B2). Since at 3 years CA there is no regular follow-up within clinical care, study-specific appointments will be made at the academic hospital or in the form of home visits. In addition, the children at risk of VPD who have been referred to the visual advisory center will undergo the VFA again (D2) as part of standard care.

By embedding the majority of this study within standard clinical care, by closely collaborating with involved medical and visual (re)habilitation specialists, and by planning participation together with regular appointments or in the form of home visits, we expect to maximize participants’ completion of the follow-up measurements.

### Intervention: visual habilitation protocol (Additional file 3)

We developed a structured visual intervention protocol using a two-step approach – (1) dissecting available scientific knowledge about visual interventions in young children and (2) establishing other, clinically relevant, factors in close collaboration with experienced behavioral therapists and neuropsychologists.

First, based on the available (visual) intervention literature, we extracted several key features for the intervention, thus constructing a protocol with the following characteristics:
Starts well before school age to maximize experience-dependent neuroplasticity [38, 39]Involves the total spectrum of visual development, not restricted to only a few visual functions [40] or general neurodevelopment [41]Has quantitative and functional outcomes [23, 28]Employs two intervention strategies that have complementary value [20, 27]:
Passive (bottom-up-feedforward) visual stimulation that is purposeful and specific [42–44]Active (top-down modulated) visual perceptual training that is contingent on children’s abilities [28, 43, 45]Can be individually tailored by adapting materials and activities to children’s preferences and capabilities [25]Incorporates children’s systems through active caregiver involvement [38, 46]

Second, we examined the clinical and practical requirements for an intervention protocol by consulting professionals about which types of habilitation to include, in which (developmental) domains, which elements, materials and objects to use, minimum duration and frequency, and how to handle parental motivational and resistance issues. The answers to these questions were grouped and analyzed in order to extract common themes and select the most important clinical features the protocol should contain.

The result of this two-step process is a visual intervention program that consists of:
A general protocol that is identical for all childrenA supplement protocol that is tailored to the specific VPD of the child.

Both parts are designed to adhere to the child’s basic visual skills and to their cognitive, motor and socioemotional developmental level. Importantly, the parent–child relationship will be taken into account in order to support, involve and stimulate the parents in executing the intervention program at home.

The general visual protocol is adapted to the child’s age and developmental level and consists of exercises focused on the following functions: fixation, pursuit, visual attention, enhancing visual experiences and knowledge, perception of details and combining vision with motor action (visuomotor skills). The intervention program consists of several steps that can be applied to all functions:
Enhancing the diversity of training with different visual materialsEnhancing the duration of visual trainingDeveloping increasingly complex visual skills and behavior that are ecologically valid, i.e., related to the child’s activities and daily environment [20].

Visual input is provided in the form of different visual materials of different visual modalities (colors, black-white, moving and static objects, light and dark). The nature of visual input will be adapted to the preferences and abilities of the child, and successful responses and behavior will be rewarded (based on operant conditioning). Visual training of more complex skills and behavior is done by teaching the child to use a specific visual skill, to expand its use to other tasks and to integrate it in everyday life.

The supplement visual protocol is designed around the specific VPD that are determined based on results of the visual screening and assessments (VFA and observation) performed at baseline. For example, children with abnormal processing of form and motion information, but with normal processing of contrast and color information, will get additional training for the processing of form and motion-related visual information that is integrated within the visual intervention program itself in order to comprehensively support the child.

Additional components:
Focus moments. These therapy sessions with video feedback, evaluation with the parents and reports of behavioral observations, are done three times throughout the intervention period to determine whether the program suffices or needs adaptations.Stepping cards (per therapy session). An instruction for the daily practice sessions of parents that contains a specific goal, instruction, observational points, and evaluation.Logbook for therapists (per session) and parents (to be completed weekly). The logbooks are used to keep track of the frequency, intensity and content of the therapy sessions and the daily practice sessions by parents.Protocol for Activities & Materials to be used, based on chapter 5 [29]

### Criteria for discontinuing or modifying interventions

Modifying the intensity of intervention: after the second focus moment (around week 16), it will be determined whether the child will still benefit from weekly sessions or could have these every 2 weeks. If this intervention intensity is no longer needed, the intensity is brought down to once every 4 or 6 weeks, to keep monitoring (visual) development, and to enable another frequency adaptation when needed. This will be done until the end of the program.

Modifying the content or focus of rehabilitation: this is based on the evaluations with parents and the observations after each therapy session. If a modification is warranted, only the supplement protocol will be modified, the standard protocol will not change.

### Improving and monitoring intervention adherence

All intervention activities are demonstrated and explained to the parents by the therapists. The goal is to have them understand the content of activities and the underlying motivation, to stimulate parents to practice daily with their child. Parents will participate in all therapy sessions – they do not only receive practice instructions but will also be educated on the visual development of their child. The parents are asked to log their daily practice session in order to evaluate them in the therapy sessions. These evaluations will give insights in improvements and/or changes in visual performance of the child, which is known to motivate parents and enhance intervention adherence.

### Permitted concomitant care

Participating children will not be restricted in receiving care as usual. If applicable, they are allowed to engage in additional neurodevelopmental training programs during this study. However, participation in such programs will be carefully registered and monitored to consider interference with the possible effects of the visual intervention program. In addition, children in the control intervention group will be provided with general developmental support and monitoring that does not include specific visual training components. This program consists of visits by a psychologist-in-training (under supervision of neuropsychologists from the academic hospital and visual advisory center) and aims at monitoring developmental achievements of preterm children from 1 to 2 years of CA. That way, we directly involve all parents in the study, and enable a structured and controlled investigation of the effectiveness of specific visual habilitation. After concluding the study, the children who are at risk of VPD and have been referred to the visual rehabilitation center will continue to be monitored there. This means that their treatment does not necessarily stop, but that this depends on the indications and judgement of the therapists and psychologists.

### Outcome measures

To answer our main research question about the effectiveness of early visual intervention in young preterm children, we will compare visual outcomes between the intervention and control group. We will analyze results from the eye tracking-based visual assessment and the additional VFAs at baseline and at yearly follow-up measurements. Primary outcomes are the changes in visual parameters after the duration of the intervention study (i.e., from baseline to follow-up T1 and/or T2), namely quantitative visual parameters (eye tracking-based visual detection and viewing reaction times) and VFA (visual acuity, contrast sensitivity, visual field, ocular motility).

Endpoints are the changes in these parameters after the visual intervention program. These parameters are chosen since their combination provides quantitative and objective results about functional viewing behavior (the eye tracking-based assessment) and clinically relevant visual function outcomes (i.e., the VFAs). In addition, we will compare the effectiveness of direct (at 1 year CA) versus postponed visual habilitation (at 2 years CA) by comparing visual outcomes between these groups at T2.

Secondary outcomes are the neurodevelopmental level at the first follow-up (T1) and results from parental questionnaires about daily visual functioning at T1 and/or T2, i.e., total score, cognitive and motor sub scores of the neurocognitive assessment with Bayley Scales of Infant and Toddler Development (Bayley-III-NL) and total score and sub scores per visual domain of the PAI-CY 0–2 Inventory (i.e., attachment, stimulus processing, orientation, play, mobility, communication). These measures were chosen because Bayley-III-NL is the only available neurocognitive assessment for children at this age, and the PAI-CY 0–2 Inventory is the only available parental questionnaire about daily (visual) behavior at this age.

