#### Intervention

For a detailed outline of the visual rehabilitation protocol we refer to the section ‘Intervention: a visual habilitation protocol’ and to Additional file 3: template visual intervention protocol. To reliably examine the effectiveness of the visual intervention program with an RCT, children who are at risk of VPD will be randomly allocated to one of two groups, as follows:
*Intervention group (direct)*

This group consists of very preterm children who are at risk of VPD and who will start the visual intervention program upon referral to the visual rehabilitation center (i.e., around 1 year CA). The program consists of a general protocol (standardized across participants) and a supplement protocol (tailored to the child’s specific VPD), and lasts ~ 1 year.
2.*Control group (postponed and placebo)*

This group consists of very preterm children who are also at risk of VPD, but for whom the visual intervention program will be postponed for the duration of 1 year. These children will be placed on a waiting list for the duration of the direct visual intervention (i.e., ~ 1 year). During this first year, they will receive a placebo intervention involving general developmental support that is aimed at monitoring the child’s developmental progress without providing specific visual habilitation. As soon as the follow-up assessments of the direct intervention group are completed, children in the control group will start visual intervention (i.e., around 2 years CA).

Importantly, this study design ensures that all children at risk of VPD will receive visual intervention at an earlier age than is the case in current standard care (i.e., where only a small number of young children will be referred based on obvious ocular disorders, and others will not receive interventions before the age of 4–6 years), while the RCT design enables a reliable and controlled comparison of the effectiveness of visual intervention within this group.

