##### Visual screening – A0

All included children will be screened for a risk of VPD, which consists of (1) an eye tracking-based assessment and (2) a neurological checklist. The eye tracking-based assessment is used to measure visual attention and processing functions. The assessment will be combined with an existing appointment for standard outpatient visits at the Neonatology Department when the child is ~ 1 year CA (T0) and 2 years CA (T1). During this assessment, children sit in front of the eye tracker monitor at a distance of approximately 60 cm, either independently, on the lap of their parent or in a pram. They do not receive verbal instructions and their body and head position is not restricted. The assessments are conducted in a quiet room with ambient light conditions. Visual stimuli (images and movies) are presented on the monitor to engage the reflexive orienting eye movements of the child, while simultaneously the eye positions are recorded over time using infrared cornea reflection (Tobii T60 XL or Tobii X3, Tobii Corporation, Danderyd, Sweden). That way, the child’s eye movement responses to various types of visual information (i.e., contrast, color, motion and form) are automatically recorded. These viewing behavior responses indicate whether and how fast a specific stimulus was detected and looked at. From these responses, the number of detected stimuli and the reaction time to fixation (RTF) of a stimulus are calculated. RTF is a measure for the timing of detecting and processing visual information and is the main study parameter [12, 13, 30, 31]. Total test duration is approximately 15 min. The child’s viewing behavior parameters per visual stimulus are analyzed and compared with normative data, i.e., developmental trajectories of an existing database of healthy control children, born at term to identify abnormal detection and timing of processing of the visual stimuli. This results in a classification of normal and abnormal visual attention and processing functions.

Second, medical specialists examine the child’s medical history for the presence of neurological risk factors for VPD in the context of prematurity [32–35], i.e., moderate-severe damage on neonatal MRI scans; cerebral palsy, unilateral/bilateral hemiplegia/diplegia; infantile esotropia/convergent strabismus or nystagmus; and deviating head circumference (> 1 SD in 12 months).

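### The outcomes section names six visual parameters at T1 and/or T2 as primary, while the analysis section makes change in RTF from T0 to T1 the single primary analysis and the rest secondary

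*Protocol article*

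**What the plan says.** Two parts of the protocol article define what is primary.

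- **Outcome measures.** The definition opens: "Primary outcomes are the changes in visual parameters after the duration of the intervention study (i.e., from baseline to follow-up T1 and/or T2". The same sentence goes on to spell out which parameters are meant: "namely quantitative visual parameters (eye tracking-based visual detection and viewing reaction times) and VFA (visual acuity, contrast sensitivity, visual field, ocular motility". That is six parameters and one or two visits. The secondary outcomes listed there are the Bayley-III-NL and the PAI-CY only.
- **Statistical analyses, Sample size calculation.** "we use a repeated measures analysis of variance (ANOVA) for the parameter RTF as primary analysis". The power calculation (N = 32, power 0.81, critical F 4.17) refers to this analysis.
- **Effectiveness of visual intervention program.** "differences in viewing behavior parameter RTF between T0 and T1 are analyzed with a Repeated Measures ANOVA", and a *p* "value of 0.05 will be considered statistically significant".
- **Other effects of visual intervention on VPD.** "Secondary study parameters are the differences in other eye tracking-based parameters of viewing behavior and the outcomes of VFAs". The 0.05 level applies again. Bonferroni is applied only to post-hoc comparisons among the five visual stimuli.
- **Visual screening – A0.** RTF "is the main study parameter".

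On the meaning of the visits, the Intervention section says: "As soon as the follow-up assessments of the direct intervention group are completed, children in the control group will start visual intervention". Until then the control group has a placebo program of general developmental support.

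**The concern.** Five of the six parameters that are primary in the outcomes section are secondary in the analysis section, and the visit is fixed in one place and open in the other. The article does not rank the six or say whether one or all must succeed. Readers use the outcomes section to judge whether a trial reported what it planned. As written, a report that led with contrast sensitivity at T2 could cite that section as support, and so could one that led with RTF at T1.

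The visit matters as much as the parameter. At T1 the randomised arms differ in visual program versus placebo program. At T2 both have had the visual program, so the contrast is early versus postponed start. A null T2 result would be compatible with a program that works at both ages, and it would not bear on effectiveness against placebo.

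**Working it through.** **1. The definitions side by side**

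| | Outcome measures | Statistical analyses |
|---|---|---|
| RTF / viewing reaction times | primary | primary |
| Detection | primary | secondary |
| Acuity, contrast sensitivity, visual field, ocular motility (VFA) | primary | secondary |
| Visit for the primary | T1 and/or T2 | T0 to T1 |

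**2. What the stated sample size supports**

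With N = 32 in two groups, the error degrees of freedom are 32 − 2 = 30. F(0.95; 1, 30) = 4.171, which matches the stated critical F of 4.17. The calculation therefore fits one test with one numerator degree of freedom at an unadjusted 0.05, which is the single-primary reading.

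The power of 0.81 cannot be reproduced from the article, which gives no effect size or within-child correlation. It is attainable: a group-by-time effect with two measurements, assumed f = 0.20 and assumed correlation 0.7 gives 0.807 at N = 32.

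**3. Error rate if the outcomes section governed**

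Assumptions: each test at 0.05, any one significant result counts as success, and no true effect. For k independent tests the chance of at least one false positive is 1 − 0.95^k.

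- k = 6 (one visit): 1 − 0.95^6 = 0.265
- k = 12 (six parameters × two visits): 1 − 0.95^12 = 0.460

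The documents give no correlations between parameters. Simulating equally correlated normal test statistics (400,000 draws, two-sided 0.05) gives:

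| Assumed pairwise correlation | 0 (formula) | 0.3 | 0.5 | 0.7 |
|---|---|---|---|---|
| 6 tests | 0.265 | 0.241 | 0.208 | 0.163 |
| 12 tests | 0.460 | 0.398 | 0.318 | 0.232 |

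For RTF from T0 to T1 as one test, the rate is 0.05.

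**4. What keeping all the primaries would cost**

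Power 0.81 at N = 32 implies a noncentrality of 8.60. Assume the same effect for every parameter and scale the noncentrality by N/32.

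- Six primaries, Bonferroni 0.05/6 = 0.0083: power at N = 32 is about 0.55, and about 50 children are needed for 0.80.
- Twelve tests, Bonferroni 0.05/12 = 0.0042: power is about 0.45, and about 56 children are needed.

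The article expects about 50 eligible children (50% of 100). Six Bonferroni-adjusted primaries would use all of them with no margin for withdrawal, and twelve tests would need more.

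**The case against.** The strongest reply is that the plan is less open than the outcomes paragraph suggests. The screening section, the sample size section and the effectiveness section all favour RTF, the last of these fixes T0 to T1, and the critical F fits one unadjusted test. On this view the outcomes section is loosely worded beside a consistent analysis section. That stands, and it shows which way to reconcile the two. It does not remove the conflict, because the outcomes section still calls the other five parameters primary.

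The T2 wording has a plausible innocent source. The Postponed intervention section says the study lasts one or two years depending on the group, and Outcome measures separately describes T2 as the comparison of direct with postponed habilitation. So the wording need not mean a free choice of visit. This also stands, but T2 remains inside the primary definition.

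Masking helps. Under Blinding and Data management, arms are recoded before the follow-up results are analysed, and allocation is revealed only after the analyses are finished. This limits selection by direction of effect. It does not prevent p values from being compared across outcomes and visits.

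A reader might infer that the headline result is simply open to choice once the data are seen, or that the trial runs a 27% or 46% error rate. The documents do not support either. A single primary analysis is named, and nothing suggests an intention to select. The two percentages also need three conditions: that the outcomes section overrides the analysis section, that any one result suffices, and that the tests are independent. No section states the second; the outcomes section says the parameters were chosen for what they show in combination. The third is unlikely for the same parameter measured in the same child at T1 and T2.

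**Conclusion.** The article is wrong as written on this point: its outcomes and analysis sections give different primary outcomes in both parameter and visit, and nothing reconciles them. The weight of the text supports change in RTF from T0 to T1 as the single primary, for which the error rate is 5% and the stated N applies.

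The exposure is conditional. It is about 16–27% for six parameters at one visit and 23–46% for twelve tests, and only if the outcomes section governs and any single result counts. The ranges rest on an assumed common correlation between 0.7 and 0.

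One gap remains even under the RTF reading. RTF is obtained per stimulus, the analysis section refers to five stimuli, and no summary across them is named, so RTF alone is not yet a single endpoint.

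**What to change.** In Outcome measures:

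1. State one primary outcome: the change in RTF from T0 to T1, compared between the randomised arms (the group-by-time effect), with one stated summary across the five stimuli. Keep the change from baseline, which both sections already specify.
2. Move detection and all VFA parameters to secondary, as the analysis section already does.
3. Remove T2 from the primary definition and list it as the secondary comparison of direct with postponed start.

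Make the same change in the analysis plan and registry entry if they carry the same definition, and date it before the follow-up data are analysed.

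The cost is wording only, with no new data. The VFA outcomes lose primary status. The stated N = 32 and power 0.81 are not changed by this fix. If the sponsor does want several primaries, it should state a multiplicity rule and redo the sample size.
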